### Intervention

The CORAL decision aid was originally developed in the UK [21, 23, 24] and was first tested in 2013. In that RCT, using CORAL among unemployed people with MHI more often led to full-time employment and less decisional conflict than in the control group [24]. The current study examines the effects of the CORAL decision aid in the Netherlands. For this study, CORAL has been modified to provide a newer version for the Dutch context, CORAL.NL, and has been extended with two infographics and newly developed training targeted at employment specialists.

### CORAL.NL

In 2017, prior to this study, the CORAL decision aid was translated and developed further to fit into Dutch practice. To attain this, focus groups were held with (1) people with MHI, (2) employers, (3) human resource managers, (4) mental health advocates and (5) employment specialists [18]. The new CORAL.NL decision aid was tested and implemented in pilot tests. Contrary to the original UK CORAL decision aid, which is designed for independent use, the Dutch CORAL.NL decision aid is a comprehensive module in which people with MHI and their employment specialists are able to discuss disclosure of MHI in the work context, so that informed decisions can be made and implemented. CORAL.NL consists of four parts with several paragraphs: Part 1 deals with choices about disclosure and contains the pros and cons of disclosure and the personal disclosure needs and values. Part 2 is about one’s personal situation and deals with questions about when and to whom disclose should be made. Parts 3 and 4 summarize previous sections to make a plan about whether to disclose or not, and if so, to whom and when and what to disclose. In addition to CORAL.NL, for this study two one-page infographics have been developed that summarize the most important information from CORAL.NL: one version about disclosure during the job application process and one version about disclosure in the work context for people who already have employment. These infographics provide an easy to read one-page summary of the CORAL.NL booklet and were developed because during a pilot test, some respondents found it difficult to use the CORAL.NL booklet itself as they had trouble reading or concentrating.

### Intervention/training-based care

Employment specialists who are allocated to the intervention group receive workplace stigma-awareness training about disclosure of MHI in the work context, from the start of this study. This training is specifically designed for the purpose of this study and consists of three meetings within 6 months. Each meeting has a duration of 2 h and is provided in groups of 4–12 employment specialists under guidance of 2–3 trainers. The aim of the training is to enhance awareness of stigma, discrimination and the disclosure dilemma and to introduce the CORAL.NL tools (including the booklet and infographics). Factors that contribute to reducing stigma and discrimination using training interventions are education and social contact between people with and without MHI [31]. Therefore, informative presentations are given during the training sessions, people with lived experiences are present, a film is shown in which people with lived experienced share their experiences and feelings about stigma and discrimination in the work context, discussions take place and using role-play, employment specialists have the opportunity to practice what they learn. After the first meeting, employment specialists have the skills to use the CORAL.NL tools. Several aims are addressed: (1) creating awareness of stigma and discrimination in the work environment by providing insight into what stigma is, how it works and how it can be experienced and what the effects of stigma are; and increasing insight into stigma and discrimination by employers and managers, the effects of employment specialists’ own attitudes, personal prejudices and actions and to increase insight into the negative effects of disclosure in job applications; (2) increasing understanding of how the disclosure dilemma can be experienced by people with MHI, how it affects people and how the conversation about disclosure can be started, without influencing the outcome and (3) learning to work with the CORAL.NL tools, including how they can be used in daily practice and experiences of working with the tools. Employment specialists are stimulated and reminded to use CORAL.NL after participants have completed T0 (baseline).

### Support as usual

Participants in the control group receive support as usual from their employment specialists. Neither participants nor employment specialists are introduced to CORAL.NL. In the Netherlands, people who receive social benefits from their municipality, have the responsibility to (re-)integrate into employment. Municipalities offer various facilities such as guidance from employment specialists, education and training.

### Procedure

#### Randomization of employment specialists (ES)

All 72 participating employment specialists were recruited between November 2017 and March 2018 from eight participating organizations. Two researchers presented the study during meetings at the local organizations, provided written information about the study and provided a registration form and informed consent form. After including all employment specialists, the organizations were randomly allocated to either the intervention or control condition, using SPSS software. Cluster randomization was chosen, as individual randomization would have higher risk of contamination between the intervention and control group, because employment specialists within organizations work together on a daily basis. Due to the nature of the intervention, neither the employment specialists nor the researchers can be masked to the allocation to the conditions.

#### Recruitment of participants

Participants are recruited via the employment specialists working at eight different organizations, and via newspapers and personal letters from the organizations. Inclusion criteria for the study are (1) being unemployed, (2) having sought any treatment (currently or in the past) for MHI, including addiction, by a health professional (e.g. general practitioner (GP), psychologist) and (3) adequate command of the Dutch language, as the intervention and questionnaires are in Dutch. Employment specialists are asked to provide people who meet the inclusion criteria with information about the research and to ask if they are willing to receive more information about the research. If participants give permission to share their contact details with the researchers, they are informed about the research by telephone and the inclusion criteria are checked.

### Outcomes

Table 1 presents an overview of the collected data and the study time path.

**Table 1 Tab1:** Data collection and time path

Topic	Instrument	Baseline	Follow up		
		T0	T1	T2	T3
			3 months	6 months	12 months
**Primary outcomes**					
Cost-effectiveness of the intervention	TiC-P EQ-5D-5 L	X	X	X	X
Having employment (yes/no)	Data from Statistics Netherlands^a^ Municipal administration Questions about work, income and benefits	X	X	X	X
Days from baseline until start employment (*n*)		X	X	X	X
Receives social benefits (yes/no)		X	X	X	X
Having other forms of employment (i.e. voluntary work)		X	X	X	X
Decision making about disclosing MHI	DCS Stage of decision making	X	X	X	X
**Secondary outcomes**					
Mental health	PHQ	X	X	X	X
Wellbeing	WEMWS	X	X	X	X
Stigma	ISMI-10	X	X	X	X
Discrimination	DISC (shortened version)	X	X	X	X
Work-related factors	Job seeking activities Personal fears about getting to work RTW-SE PSWOHP (shortened version)	X	X	X	X
**Prognostic measures**					
Age, gender, nationality, marital status, level of education		X			
History of mental ill-health		X	X	X	X
Characteristics of work and/or social benefits		X	X	X	X
**Additional measures**					
Work values/core capabilities	Core Capability Set	X	X	X	X
Characteristics of employment specialists	Age, education, years of work experience of employment specialists OMS-HCP	X			X
Personal experiences and satisfaction with CORAL.NL^b^	Questions about the use of the decision aid Interviews with employment specialists and participants in intervention group	X	X	X	X

*TiC-P* Treatment Inventory Costs in Psychiatric Patients, *EQ-5D-5 L* Euroqol-5 dimensions-5 levels, *DCS* Decisional Conflict Scale, *MHI* mental health issue/illness, *PHQ* Patient Health Questionnaire, *WEMWS* Warwick-Edinburgh Mental Wellbeing Scale, *ISMI-10* Internalized Stigma of Mental Illness, *DISC* Discrimination and Stigma Scale, *RTW-SE* Return To Work Self Efficacy Scale, *PSWOHP* Patient Satisfaction With Occupational Health Professionals scale *OMS-HCP* Opening Minds Scale for Healthcare Providers

^a^ If participants agree with access to personal data from Statistics Netherlands, data are also collected from baseline to T3 if they discontinue to fill out the questionnaire

^b^ Only for participants in the intervention group

#### Primary outcomes

The primary outcomes of this study are (1) cost-effectiveness, which will be measured from a societal perspective comparing the intervention with usual care. Healthcare utilization and loss of production will be measured using the Treatment Inventory Costs in Psychiatric Patients (TiC-P), which is a reliable instrument with satisfactory validation [32]. The primary cost-effectiveness outcomes are having employment (yes/no), days from baseline until start employment, receiving social benefits (yes/no) and/or having other forms of employment (i.e. voluntary work, internship). The secondary cost-effectiveness outcome is the EuroQol-5D-5 L, which measures health-related quality of life [33], and (2) decision making about disclosing MHI, measured using the Decisional Conflict Scale, which has adequate test-retest reliability [34], and stage of decision making [35].

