**Methods:**

This is a two-armed, clustered, randomized controlled trial with longitudinal design and randomization at organization level. An intervention will be examined, which consists of a disclosure decision aid tool (CORAL.NL) for unemployed people and workplace stigma-awareness training especially designed for employment specialists, which focusses on how to support unemployed people in their disclosure decisions. Participants in the intervention group are unemployed people who receive support from trained employment specialists from organizations allocated to the intervention group, and receive the CORAL.NL decision aid after baseline. The control group consists of unemployed people who receive support as usual from employment specialists from different organizations allocated to the control group. Primary outcomes are: cost-effectiveness of the intervention, e.g. healthcare costs, having employment, days until start of employment, independency of social security, having other forms of employment and decision making about disclosing MHI. Secondary outcomes are mental health and wellbeing, stigma and discrimination and work-related factors. Financial income data are collected via the registration systems of Dutch municipalities and Statistics Netherlands, and by questionnaires at baseline, and at 3, 6 and 12 months.

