### Objective and research questions

An RCT is conducted to examine the effects of an innovative intervention based on the English CORAL decision aid [23], which has been adapted to the Dutch context and embedded in an intervention for unemployed people with MHI and workplace stigma-awareness training especially designed for employment specialists. Furthermore, factors that facilitate finding employment and factors that hamper this will be studied. The primary research questions of this study are:
Does the intervention more often lead to finding and retaining paid employment for unemployed people with mental health problems, compared to usual guidance in municipal practice, controlled for other factors (e.g. mental health and stigma and discrimination)?Is the intervention cost-effective from a societal perspective (including reintegration costs and healthcare costs)?For whom, under which circumstances and in what way does the intervention work best or less well, and why?

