### Sample size

The power calculation is based on data from a recent international study on individual placement and support, which is an evidence-based reintegration model that is also used for people with MHI who want to have regular employment [45] and has the same primary outcome measure, i.e. obtaining employment. In this study, the average percentage employment was 50% in the intervention group and 20% in the control group [45]. Considering 50% and 20% as possible percentages, 36 unemployed people are needed in each group to find a statistically significant difference (with a 5% significance level and power of 80%): 47 participants per group would be needed for power of 90%. However, in this study any cluster effects and the expected dropout of participants over the four measurements must be considered. Considering a dropout rate of approximately 40% because of the vulnerable population, a safe assumption is to have 75 participants per group, which means a total of 150 participants.

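### Six outcome rows are called primary with no lead outcome or main time point, while the sample size section treats obtaining employment as the one primary outcome

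*Protocol article*

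**What the plan says.** The primary outcome is described in five places in the protocol article.

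- **Abstract, Methods.** The list opens with "Primary outcomes are: cost-effectiveness of the intervention, e.g. healthcare costs, having employment, days until start of employment, independency of social security" and continues with other forms of employment and disclosure decision making. It is introduced by 'e.g.', so it is not closed.
- **Table 1.** Six rows stand under the primary heading: cost-effectiveness, employment, time to employment, social benefits, other forms of employment, and disclosure decision making. The last row has two instruments, the Decisional Conflict Scale (DCS) and stage of decision making. Every row is marked at T0, T1, T2 and T3.
- **Primary outcomes.** There are two numbered domains. The first is introduced by "The primary outcomes of this study are (1) cost-effectiveness, which will be measured from a societal perspective", and within it "The primary cost-effectiveness outcomes are having employment (yes/no), days from baseline until start employment, receiving social benefits (yes/no) and/or having other forms of employment", with voluntary work and internships as examples of the last. Only the EQ-5D-5L is ranked lower, as the secondary cost-effectiveness outcome. The second domain is "2) decision making about disclosing MHI, measured using the Decisional Conflict Scale", together with stage of decision making.
- **Sample size.** The reference study is said to share this trial's primary outcome: it "has the same primary outcome measure, i.e. obtaining employment". The calculation uses that outcome alone.
- **Objective and research questions.** Question 1 reads "Does the intervention more often lead to finding and retaining paid employment". Cost-effectiveness from a societal perspective is question 2.

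The Statistical analysis section gives one general method, longitudinal multilevel analysis, for all outcomes.

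**The concern.** The sections fix the primary outcome in two incompatible ways: an unranked list in the abstract, Table 1 and Primary outcomes, and a single outcome in Sample size. The 'and/or' among four of the listed measures leaves open whether one, some or all of them decide the result. No section says which outcome leads, at which follow-up time, or how many must succeed.

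Without that statement, the 5% level used to size the trial does not govern the trial's main claim. A difference seen only in unpaid work, or only in decisional conflict, could be reported as a positive primary result, although the first research question is about paid work and only employment was powered. Registration took place in June 2019, with recruitment running from April 2018 to July 2019, so it came too late to serve as a prior commitment. What the register entry says cannot be checked here.

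**Working it through.** **1. Which outcome the sample size rests on.** Inputs from Sample size: 50% versus 20% employed, 5% level, 80% or 90% power. The document does not state sidedness or formula. Two-sided with unpooled variance:

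n = (z_0.975 + z_power)² × (0.5×0.5 + 0.2×0.8) / 0.3²

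- 80% power: 35.76, so 36 per group (stated 36).
- 90% power: 47.87, so 48 per group (stated 47, a rounding difference).

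The stated figures therefore follow from employment alone. No other listed outcome enters.

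**2. How many tests the list could imply.** Six rows stand in Table 1. If cost-effectiveness is estimated rather than tested, as is usual, five remain. Counting the DCS and stage of decision making separately adds one to either count.

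**3. Chance of at least one false positive if any one success counts.** Assumption: each outcome is tested at two-sided 5%. The document states 5% only for the sample size and gives no other allocation.

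- Five independent tests: 1 − 0.95⁵ = 22.6%.
- Six independent tests: 1 − 0.95⁶ = 26.5%.
- All seven measures tested: 1 − 0.95⁷ = 30.2%. This needs a significance test of cost-effectiveness as well as both instruments, so I do not rely on it.

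The outcomes are plainly correlated, but the document gives no correlations. The table assumes a range, with six equally correlated normal test statistics, by simulation with 400,000 draws:

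| Assumed correlation | Any significant result | Any result favouring the intervention |
|---|---|---|
| 0 | 26.5% | 14.1% |
| 0.3 | 24.1% | 12.2% |
| 0.5 | 20.7% | 10.3% |
| 0.7 | 16.4% | 8.2% |
| 0.9 | 10.8% | 5.4% |

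The values for a single outcome are 5% and 2.5%.

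**4. What each reading means for size.**

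- *One primary outcome:* the level stays at 5% and the figures in step 1 stand.
- *All six primary, any one sufficient, Bonferroni:* 0.05/6 = 0.0083. The same formula gives 56 per group at 80% power. With the stated 40% dropout, 56/0.6 = 93.3, so 94 per group against 75 planned.
- *Power with 75 × 0.6 = 45 completers per group:* 88% at the 5% level and 69% at 0.0083.

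All of step 4 is before any cluster effect.

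**The case against.** The strongest reply is that the intent is clear enough. Research question 1 and the sample size both point to employment. Trial status says the primary outcome data come from Statistics Netherlands and stay out of the researchers' reach until three months after the last measurement. The numbered domains give some structure, and an analysis plan that is not shown may set a testing procedure.

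Much of this stands, and it rules out several stronger readings that a reader might infer:

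- *That 'and/or' joins the whole list.* It joins only the four employment and benefit measures, which are the effect measures of the economic evaluation.
- *That every outcome is tested at 5% at each of three visits, giving 18 tests and 1 − 0.95¹⁸ = 60%.* No section says so. A longitudinal multilevel model normally takes the visits together, and time to employment is one duration per person.
- *That unpaid work is merged into paid employment.* Table 1 keeps them on separate rows. The issue is only that unpaid work has equal primary standing.
- *That the absence of a multiplicity procedure is itself a fault.* That is commonly left to the analysis plan.

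The conflict remains. Intent inferred from two sections does not overrule three others that list the outcomes as equals, and the numbers (1) and (2) are labels, not a testing order. The delayed access protects register outcomes only. The DCS and stage of decision making are questionnaire measures collected in appointments with project researchers, who are not masked to allocation.

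**Conclusion.** The point holds as a conflict within what the protocol itself fixes. Six rows, or seven measures, are primary without a lead outcome or a main time point, against a single powered outcome in the Sample size section.

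The size is an upper range, not a property of the plan. It rests on two assumptions, that any one success suffices and that each outcome is tested at 5%. The inflation shrinks as the outcomes overlap more, but within the assumed correlations it stays above the nominal level. The choice should be settled before the register data are retrieved, because afterwards it could not be shown to be independent of the results.

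**What to change.** Reconcile the abstract, Table 1, Primary outcomes and Sample size sections before the register data are retrieved:

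1. Name paid employment (yes/no) at one stated time point, for example T3, as the single primary effectiveness outcome.
2. State its data source, including what is used for participants who do not give the separate consent to Statistics Netherlands linkage. Table 1 also allows municipal records and questionnaires.
3. Make time to employment, social benefits, other (unpaid) forms of employment, the DCS and stage of decision making secondary effectiveness outcomes, and delete 'and/or'.
4. Keep cost-effectiveness as a separate primary economic question, in line with research question 2, reported as an estimate with its uncertainty.

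The cost is rewording; the sample size calculation is untouched. Some outcomes lose the primary label. Employment status at one time point does not by itself capture retention, which research question 1 also asks about, so a secondary measure of retention is needed.

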#### Secondary outcomes

Secondary outcomes will be explored as follows:
Mental health is measured using the Dutch version of the Patient Health Questionnaire [36–38], which is used to measure the most common psychological diagnoses (mood disorders, anxiety disorders, alcohol abuse, somatoform disorders and eating disorders), and has good diagnostic validity [36].Wellbeing is measured using the Warwick-Edinburgh Mental Wellbeing Scale [39], which measures positive mental wellbeing and has good content validity and test-retest reliability.Stigma is measured using the brief Internalized Stigma of Mental Illness Scale-10 [40], which measures self-stigma among people with MHI and has good internal consistency.Discrimination is measured using two items of the Discrimination and Stigma Scale [15], which focuses on discrimination when finding and keeping employment.Work-related factors such as job-seeking activities are measured using four items, e.g. “Have you applied to a job vacancy in the last four weeks?”; personal fears about getting to work are measured using five items with a 5-point Likert scale, e.g. “Because of my mental health issues/illness, I have less opportunities finding employment”; work-related self-efficacy is measured using the Return to Work Self-Efficacy scale [41], which has good internal consistency and adequate test-retest reliability; and finally, the quality of guidance from employment specialists is measured using three items of the Patient Satisfaction With Occupational Health Professionals scale [42].

### Prognostic measures

The following prognostic data will be collected: personal characteristics such as age, gender, nationality, marital status, level of education and history of mental and physical ill-health.

### Additional measures

A variety of factors that can be influenced by the intervention or can affect the chances of finding employment are also measured:
Core capabilities are measured using the Core Capability Set [43], which assesses the capabilities that are important for individuals (what they value) in relation to employment: this is a validated measurement. An adapted version of the Core Capability Set is used for participants without employment.Employment specialists receive two short questionnaires, i.e. at the beginning of the research and after including all participants, which contains questions about their demographics (age, education, years of work experience), experiences with people with MHI and attitudes towards people with MHI, measured using the Opening Minds Scale for Health Care Providers [44], which has good internal consistency and satisfactory test-retest reliability.Process evaluation: experiences with the intervention are measured among participants in the intervention group. Questions focus on whether the decision aid has been used in recent months and participants’ opinions on the decision aid. Participants in the control group are asked at measurement T3 if they are familiar with the decision aid and if so, how they get familiar with using the decision aid and what their experiences are with the decision aid. Additionally, individual 1-h interviews are held with employment specialists and participants of the intervention group after the quantitative data collection. The interviews focus on for whom, under which circumstances and in what way the CORAL.NL decision aid work best or less well and why.

